### Inclusion criteria

Aged over 18 years oldPartial edentulism (all incisors and canines present) for at least 3 months from tooth lossResidual bone height ranging from 6 to 8 mmSufficient bone width in the edentulous region (≥6 mm)

### Exclusion criteria

Medically compromised patients (American Society of Anesthesiologists (ASA) classification III–IV)Heavy smokers (>10 cigarettes/day)Uncontrolled diabetes mellitusComplete edentulism

### Recruitment

Recruitment will be performed in the Department of Oral and Maxillofacial Implantology, Shanghai Ninth People’s Hospital. Eligible patients will receive the study information and consent forms. No patients will be included in the study until the consent forms are signed.

### Allocation and blinding

The patients will be divided into three groups using randomization tables allocating the patient a number within a corresponding envelope: group 1: short implants (6 mm) alone; group 2: short implants (8 mm) combined with OSFE; group 3: standard implants (10 mm) combined with OSFE. The assignment will be concealed from the clinical operators until the beginning of implant surgery. The outcome examiners and patients will be kept blinded to the assignment.

### Surgical procedures

For all the cases, Straumann (Institute Straumann AG, Basel, Switzerland) Standard Plus implants will be placed. Following a mid-crestal incision, a full-thickness mucoperiosteal flap will be reflected. In group 1, 6-mm implants will be inserted according to the manufacturer’s instructions. In group 2, after implant, the site will prepared to a depth of about 1–2 mm away from the sinus floor, a modification of Summers’ OSFE will be performed to elevate the sinus membrane to a depth of 8 mm. In group 3, similar procedures will be performed until the sinus membrane is elevated to a depth of 10 mm. The OSFE procedure has been described in detail previously [16]. After surgery, anti-inflammatory amoxicillin (Xinya Co., Shanghai, China, 500 mg, three times a day for 7 days) and metronidazole (Xinyi Wanxiang, Shanghai, China, 400 mg, three times a day for 7 days) will be used. In addition, chlorhexidine oral rinse (0.12 %) will be prescribed for 60 s two times a day for 14 days. A one-stage protocol will be performed. After a healing time of 3–4 months, an impression will be taken at the implant level. Straumann synOcta titanium abutments will be fixed onto the implants. Porcelain (Ivoclar Vivadent AG, Schaan, Liechtenstein) fused to noble metal (Heraeus Kulzer Corporation, Hanau, Germany) crowns and bridges will be fabricated.

### Outcomes

#### Baseline assessment

Resonance frequency analysis (RFA) measurements, treatment time and patient-reported outcome will be recorded. RFA assessment will be performed immediately after surgery, 2 weeks later and 3 months after surgery. RFA measurements will be conducted by the Osstell™ mentor (Integration Diagnostics AB, Göteborg, Sweden). Treatment time will be calculated from incision beginning to suture finishing. Patients will be asked to give their answers regarding intraoperative discomfort and postoperative pain immediately and two weeks after surgery using a 100-mm visual analogue scale (VAS) with word descriptors "very dissatisfied" to "very satisfied" on the left and right respectively.

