### Objective and hypotheses

The aim of the study is to evaluate the clinical success and the patient-reported outcome of intraoperative and postoperative pain of short implants (6 mm) alone, short implants (8 mm) combined with OSFE and standard implants (10 mm) combined with OSFE for treating atrophic posterior maxillary ridges of partially edentulous adults. Considered outcomes include implant survival rates, complications, resonance frequency analysis (RFA) measurements, marginal bone level, treatment time and patient-reported outcome (visual analogue scale for (VAS) intraoperative discomfort and postoperative pain)

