#### Follow-up assessment

All the included patients will be recalled for clinical and radiographic assessment at 12, 24, 36, and 60 months after crown placement. Survival rates, complication rates and marginal bone level will be recorded. Implant survival rates are defined as the percentage of implants still retained in the mouth. Implant success is defined according to Cochran et al. 2002 [17]. Both biological and mechanical complications will be recorded. Periapical radiographs will be taken immediately after implant surgery, and at the 1-year, 3-year, and 5-year examination. For standardization, a paralleling technique with a Rinn film holder (XCP Instruments; Rinn Corporation, Elgin, IL, USA) will be conducted. Radiographic analysis will be conducted by a software program (SIDEXIS 1.12; Sirona Dental Systems GmbH, Bensheim, Germany). Biological complications refer to peri-implant mucositis (bleeding on probing positive, and without surrounding bone loss) and peri-implantitis (bleeding on probing positive, probe pocket depth ≥5 mm and with surrounding bone loss), and technical complications are veneer ceramic chipping, framework fracture, loss of retention, screw loosening, abutment and implant fracture.

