#### Statistical analysis

Generalized estimating equations will be used to manage the correlated relationships between multiple implants in the same patient. The data of different patients are assumed to be independent. Each patient will be assigned a number, which will be an indicator (X) for primary and secondary outcome (Y). For the patient (i) and implants (j), mean model is logit(E(Yij|Xij)) = beta0 + beta1*I(Xij = 2) + beta2*I(Xij = 3), and variance model is Var(Yij|Xij) = E(Yij|Xij)*(1-E(Yij|Xij)). For patient-reported outcome (VAS), ANOVA will be used to assess the difference among the three groups. The level of significance is set at 0.05.

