## Discussion

Implant treatment in the posterior maxilla is commonly faced with great challenges due to the limited residual bone height and poor bone quality. In 2013, our study demonstrated that high survival rates can be achieved after 5–10years for Straumann SLA Standard Plus short implants (6 or 8 mm) in the posterior region, without severe marginal bone loss and complications [18]. This result shows that Straumann short 6-mm implants are predictable and reliable in the posterior maxilla. In addition, our previous studies have also indicated that the OSFE technique is also predictable and reliable in the posterior maxilla [16, 19]. Therefore, our research group is very interested in the long-term treatment outcome of short implants alone and longer implants combined with OSFE.

The results of the trial will support better decision-making for dental implant treatment in atrophic maxillary ridges. If favorable, the use of the short implant may avoid adjunct procedures used for implant insertion, thus reducing operative time, complexity and postoperative discomfort.

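### No contemporaneous pain rating is scheduled between the day of surgery and week 2, and no recall period is stated, so the postoperative pain comparison rests on the two ends of that interval or on one retrospective rating

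*Protocol article*

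**What the plan says.** The patient-reported schedule is one sentence under Baseline assessment. Patients give their answers "regarding intraoperative discomfort and postoperative pain immediately and two weeks after surgery", "using a 100-mm visual analogue scale (VAS) with word descriptors" that run from dissatisfaction to satisfaction. The sentence does not say whether the rating refers to current, worst or average pain, or over what period.

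The other relevant statements are:

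- **Aim** (Objective and hypotheses): the study is to evaluate clinical success and the "patient-reported outcome of intraoperative and postoperative pain" in the three arms.
- **Expected benefit** (Discussion, and likewise the Discussion part of the Abstract): avoiding the adjunct procedure is expected to help, "thus reducing operative time, complexity and postoperative discomfort".
- **Other early contacts** (Baseline assessment): "RFA assessment will be performed immediately after surgery, 2 weeks later and 3 months after surgery".
- **Later visits** (Follow-up assessment): patients are "recalled for clinical and radiographic assessment at 12, 24, 36, and 60 months after crown placement", with survival, complications and marginal bone level recorded and no pain item listed.
- **Analysis** (Statistical analysis): "For patient-reported outcome (VAS), ANOVA will be used to assess the difference among the three groups". No time point or summary of the ratings is named.
- **Primary outcome** (Sample size): implant survival rate, so the VAS is not primary.

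**The concern.** Postoperative pain has a course, and a comparison between arms depends on where along that course it is sampled. A rating taken as surgery ends can hardly describe the postoperative period, because almost none of it has passed. A rating at about day 14 describes either the state at day 14 or the patient's memory of the preceding two weeks, and the text does not say which.

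If the arms differ in the days after surgery and have converged by week 2, ratings at the two ends could miss the difference. A non-significant ANOVA would then have two explanations that the trial could not separate: no difference in pain, or no rating taken while the difference existed. This matters because postoperative pain is named in the aim and less postoperative discomfort is one of the advantages the authors hope to report.

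**Working it through.** No arithmetic is needed to establish the gap, and the plan gives no figure to reproduce. The check is to read the sections on visits, pain and analysis together.

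**1. Which items are asked, and when.** The sentence in Baseline assessment names two items and two times, and it can be read in two ways.

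| Reading | Immediately after surgery | Days 1 to 13 | About day 14 |
|---|---|---|---|
| Both items at both times | Discomfort and pain | None | Discomfort (by recall) and pain |
| Items and times paired in order | Discomfort only | None | Pain only |

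Under the first reading, the immediate pain rating precedes nearly all of the postoperative course, and the second discomfort rating repeats from memory something already rated. Under the second reading both of those objections disappear, but postoperative pain has a single rating. The middle column is empty either way: 13 days without a rating.

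**2. Whether another section fills the gap.** The resonance frequency contacts are on the day of surgery, at 2 weeks and at 3 months. Follow-up then resumes 12 months after crown placement, with no pain item. The article mentions no diary and no record of analgesic use.

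**3. Whether the two-week rating could cover the gap.** It could, if patients are asked about their pain since surgery. No recall period is given, so the text neither shows nor excludes this. Even then, the whole interval would be represented by one retrospective score.

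**4. What enters the ANOVA.** With two possible rating times and no time point named, the analysed pain variable is the immediate rating, the two-week rating or some combination. None of these includes a contemporaneous rating from days 1 to 13.

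**5. What is not affected.** The sample size and the main model concern implant survival. Operative time is measured directly, from incision to suture. Of the benefits listed in the Discussion, only the discomfort component depends on this schedule.

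**6. A check on the remedy.** If early ratings are added on, say, days 1, 3 and 7, the summary has to be named, because the spacing is unequal. A simple mean weights each rating 1/3. A time-normalised trapezoidal area under the curve over days 1 to 7 has intervals of 2 and 4 days, 6 in total, so its weights are:

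- day 1: (2/2)/6 = 1/6
- day 3: (2/2 + 4/2)/6 = 3/6 = 1/2
- day 7: (4/2)/6 = 1/3

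These are different variables and can give different results.

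**The case against.** The strongest reply is that a condensed article does not reproduce the questionnaire. The two-week item may ask for pain over the whole period, in which case recovery is measured, though retrospectively. This stands in part. A reader might infer that the recovery period is not measured at all, but the document does not support that. It supports only that no rating is collected during the interval and that nothing shows the two-week rating covers it. The times themselves are stated outright, so the schedule is not a detail left to a fuller document.

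Second, the sentence may pair discomfort with the immediate rating and pain with the two-week rating. This also stands. It would be wrong to assert that pain is asked before it begins, or that discomfort is rated twice. Those are consequences of one reading only.

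Third, the harm depends on when the arms differ. No section describes the time course of pain after either procedure. That differences would fall mainly in the early days is a clinical assumption, so a loss of sensitivity is possible but not demonstrated.

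Fourth, a reader might infer that the trial's whole claimed advantage for short implants is undermined. It is not: operative time is recorded separately and the primary outcome is survival.

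Finally, repeating the existing scale would not be enough. Its anchors express satisfaction, so more ratings on it would yield more satisfaction scores. This is right, and the fix has to deal with it.

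**Conclusion.** The point holds in a limited form. On either reading of the schedule, no contemporaneous postoperative pain rating exists between the day of surgery and about day 14, and no recall period is stated for the later rating. The comparison of postoperative pain, and any statement about reduced postoperative discomfort, would rest on ratings at the two ends of that interval or on one retrospective rating. A null ANOVA could then reflect timing.

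The gap is 13 days. Its effect on sensitivity cannot be calculated from the document, and the concern about a misleading null result assumes that differences between arms arise mainly in the early days. The matter is confined to an outcome that is not primary: the survival analysis, the sample size and operative time are untouched. It is a worthwhile, inexpensive improvement and not a defect that threatens the trial.

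**What to change.** - Rate intraoperative discomfort once, immediately after surgery.
- Rate postoperative pain on a short take-home VAS form on a few prespecified early days. Days 1, 3 and 7 are an example; the document does not dictate particular days.
- Collect the form at the two-week contact that the resonance frequency schedule already implies. Keep the two-week pain rating and state its recall period (pain now, or worst or average pain since surgery).
- Replace the satisfaction anchors with pain anchors for the pain item, and with matching discomfort anchors for the intraoperative item.
- Name one postoperative pain variable for the ANOVA in advance, for example the simple mean of the early ratings. Do not treat the mean and the area under the curve as interchangeable. Say whether the two-week rating is analysed separately.

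The cost is a one-page form and a small patient burden, with no extra visit. The main downside is some missing diary entries, so the plan should say how many early ratings are needed to form the summary.

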**Methods/Design:**

The proposed study is designed as a prospective single-center, three-arm parallel group, randomized controlled trial. We plan to enroll 150 patients in need of dental implant treatment in the posterior maxilla. The inclusion criteria include: age ≧18 years, partial edentulism in the posterior maxilla for at least 3 months from tooth loss, residual bone height ranging from 6 to 8 mm, sufficient bone width (≥6 mm) in the edentulous region. The patients will be divided into three groups according to a table of random numbers: group 1: short implants (6 mm) alone; group 2: short implants (8 mm) combined with osteotome sinus floor elevation (OSFE); group 3: standard implants (10 mm) combined with OSFE. The assignment will be concealed from the clinical operators until the beginning of implant surgery. The outcome examiners and patients will be kept blinded to the assignment. Implant survival rates, implant success rates, complications, resonance frequency analysis (RFA) measurements, marginal bone level, treatment time and patient-reported outcome (visual analogue scale for intraoperative discomfort and postoperative pain) will be recorded. Clinical re-evaluations will be performed at 12, 24, 36 and 60 months after crown placement.

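### The pain and discomfort VAS has satisfaction anchors, so as written it does not directly measure the pain named in the trial's aim

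*Protocol article*

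**What the plan says.** Under Objective and hypotheses, the protocol article sets out to "evaluate the clinical success and the patient-reported outcome of intraoperative and postoperative pain" across the three arms. The outcome list in the same section describes the visual analogue scale as one for "intraoperative discomfort and postoperative pain", and the Abstract (Methods/Design) uses the same description.

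Outcomes, Baseline assessment, then specifies the instrument. "Patients will be asked to give their answers regarding intraoperative discomfort and postoperative pain immediately and two weeks after surgery". The answers are marked on a 100-mm VAS with the "word descriptors 'very dissatisfied' to 'very satisfied' on the left and right respectively".

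The Statistical analysis section compares the three groups on this VAS by ANOVA at the 0.05 level. The Abstract and the Discussion both anticipate that, if results are favourable, short implants could lessen discomfort after surgery, along with operating time and complexity. The Sample size section names implant survival as the primary outcome.

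**The concern.** The named construct and the instrument do not match. The aim and the outcome list speak of pain and discomfort, while the end-points of the line are satisfaction terms. A patient can have marked pain and still be satisfied with how the operation went, or have little pain and be dissatisfied for another reason.

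Pain is named in the aim itself, and this VAS is the only patient-reported measure of it. If the anchors stay as they are, a difference between arms on this scale, or the absence of one, would be reported as a finding about pain although the patients were given satisfaction terms to mark. The anticipated conclusion on reduced postoperative discomfort depends on this measure.

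**Working it through.** No arithmetic applies. The document gives no expected difference, standard deviation or power for the VAS, and none of its stated figures depends on the anchors. The check is to set the relevant sections side by side.

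1. **Construct to be measured.** Objective and hypotheses: "patient-reported outcome of intraoperative and postoperative pain".
2. **Instrument as named.** Abstract, and Objective and hypotheses: a VAS for discomfort during surgery and pain after it. Steps 1 and 2 agree.
3. **Instrument as specified.** Baseline assessment: the question concerns discomfort and pain, but the line runs from dissatisfaction on the left to satisfaction on the right. This departs from steps 1 and 2.
4. **Search for a correction.** No other section gives intensity anchors (such as none to worst), a scoring direction for pain, or another patient-reported pain measure. The follow-up assessments from 12 months onward list survival, complications and bone level, not pain.
5. **Use of the score.** Statistical analysis enters the VAS into a three-group ANOVA. The means compared are then mean satisfaction with respect to pain and discomfort.
6. **Direction.** If the mark is measured from the left, a high value is a better experience. A pain-intensity score would run the other way. Recoding the value as 100 minus the score would turn the direction round, but it would still be a satisfaction score.
7. **Reasons other than pain for a difference between arms.** Groups 2 and 3 have sinus floor elevation added to implant placement (Surgical procedures), and the Discussion expects operating time to be shorter without it. Length of operation could move satisfaction at the same level of pain. A difference between arms on this scale therefore need not be a difference in pain.
8. **Reach.** The anchors apply to every VAS value in all three arms. The Sample size section rests on implant survival alone, so neither the primary outcome nor the sample size depends on the VAS.

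**The case against.** The strongest defence is that patients are asked about discomfort and pain, so the score is satisfaction in that respect and may well track pain. This stands in part. A reader might infer that the scale cannot answer the pain question at all, and the document does not support that. The score is an imperfect proxy for intensity, not an unrelated measure.

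A reader might also infer that a line with the good end on the right biases the comparison. That is not shown. The sides of the anchors are fixed and the same in every arm, patients are to be blinded (Allocation and blinding), and nothing suggests that misreading would differ by arm. One could attach a figure in millimetres by assuming that some share of patients mark the line the wrong way round. Both that share and the true difference would be invented, and the sum would describe flipped marks, not the use of a different construct.

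A further tempting reading is that asking only straight after surgery and at two weeks leaves the days between uncovered. The article gives no recall period for the two-week question, which could cover the whole fortnight. Such wording is commonly left to the full protocol or the form. It is no part of this point.

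Finally, it may be said that an article condenses and that the form itself could differ. But the anchors are not omitted here. They are stated, with their positions. If the form carries other anchors, the article is wrong and needs correcting.

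**Conclusion.** The point holds as a mismatch between the stated construct and the specified instrument. As written, the trial's only patient-reported pain measure records satisfaction with respect to pain and discomfort, with high values good. The ANOVA would not directly compare intensity, and any conclusion on less postoperative discomfort would be weakened accordingly.

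The effect on the VAS comparison cannot be quantified from the document. It depends on how closely satisfaction follows pain in these patients, and no figure for that is given. The finding concerns a secondary outcome only. Implant survival, its sample size and the other clinical and radiographic measures are untouched. The conclusion rests on the anchors being used as the article states them.

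**What to change.** Anchor the discomfort item and the pain item in intensity terms, for example no discomfort or no pain at 0 and worst imaginable at 100, and state the scoring direction in the protocol. If satisfaction is also of interest, keep it as a separately named scale with its present anchors.

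Trial status says that the study is open for recruitment. Any patients already scored on the satisfaction anchors should have those values reported separately as satisfaction and not pooled with the intensity scores.

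If the anchors are to be kept, rename the outcome and the matching part of the objective as satisfaction, and draw no conclusion about pain or discomfort from it.

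The cost is one reprinted form and a short protocol change. If recruitment has begun, there may be two scales that cannot be combined, so fewer patients would contribute to the pain comparison.
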